## Abstract

**Background:**

Adolescence and young adulthood are critical times of initiation and progression to daily use of tobacco. However, it is difficult to recruit young adults to traditional smoking cessation and retention rates are typically low. Smartphone cessation applications (apps) can provide real-time responses to smoking urges and related cues, which are known to be important factors in lapse and relapse. Given the popularity of smartphones among young adults and the considerably higher download rates of commercially developed apps compared to research-based apps, there is a need to design pragmatic studies that evaluate commercial tobacco cessation apps. The aims of this pilot study are to assess the impact on tobacco cessation of using a smartphone app compared with usual care and to generate feasibility data to inform a future fully powered clinical trial.

**Methods:**

We will conduct an open randomized controlled trial with parallel groups. Participants will be selected from hospitalized patients and must be aged 18–30 years, interested in cessation, smoked > 5 cigarettes/day over the past 30 days, and own an Apple or Android smartphone. Participants who are eligible will be randomized to either a smartphone experimental group or patient-initiated follow up (usual care). As this study seeks to assess feasibility, the primary data will include (1) recruitment rates, (2) retention rates, and (3) adherence, measured through user engagement with the app.

**Discussion:**

This pilot trial will be the first to evaluate a commercially available smartphone app for tobacco cessation in a hospitalized setting. Data generated by this study can be used for larger fully powered trials such as comparative effectiveness studies against apps developed by academics or health scientists based on behavioral theories, or cost-effectiveness analyses of mobile interventions.

**Trial registration:**

ClinicalTrials.gov, NCT03538678. Registered on 28 May 2018.

**Electronic supplementary material:**

The online version of this article (10.1186/s13063-019-3246-2) contains supplementary material, which is available to authorized users.

## Background

Tobacco use continues to be the leading cause of preventable death in the USA [1]. Smoking causes almost 9 out of 10 lung cancers. Indeed, the US Surgeon General’s Report notes that young adults’ smoking remains a major public health concern [2]. However, individuals who successfully quit smoking reduce their risk of death from lung cancer by half within 10 years. Although 30 million smokers contact a healthcare provider each year [3], and more than half attempt to quit, most are not successful [4]. Additionally, most available treatments are not optimized for use among the young adult population [5], and unfortunately, young adults who try to quit often relapse [6]. Adolescence and young adulthood remain critical times of initiation and progression to daily use of tobacco [7]. Nevertheless, there are barriers to effective implementation of traditional smoking cessation programs among young adults. First, it is difficult to recruit young adults into traditional programs [8], and retention rates for this population in these programs are as low as 33% [9]. Moreover, traditional program interactions between facilitators and clients are highly intermittent. This compromises the ability to provide real-time responses to smoking urges and related cues, which are known to be important factors in lapse and relapse.

Smartphones have become ubiquitous in the USA, especially among young adults. The Pew Research Center reported in 2018 that 94% of US adults age 18–29 years owned a smartphone [10]. Mobile health (mHealth) researchers have taken advantage of these opportunities: Android and Apple platforms have numerous options of commercially developed apps designed to help quit tobacco use. However, studies reviewing tobacco cessation apps have been generally descriptive [11–13], providing information such as popularity, features, or techniques used for smoking cessation. In addition, all of these reviews cite a lack of evidence-based research, and no published studies report verified information on any health outcome.

In spite of the lack of evidence, commercially developed apps for tobacco cessation are successful. In comparison, there are two apps available through smokefree.gov, in collaboration with the National Cancer Institute (NCI): QuitGuide and quitSTART. While these apps were developed through research efforts by NCI, they are not highly rated by user reviews and are less popular than commercial apps. Both QuitGuide and quitSTART have each been downloaded approximately 1/10th as many times as Kwit, a leading commercial app and the focus of the current study, according to Google Play. This poor performance of research-based apps may be due to the lack of dedicated marketing teams and/or insufficient updates, as research-based apps can depend on continued funding for support rather than profits. For example, as of this writing, neither app has been updated in several months, while top-rated commercial apps are updated every 1–2 weeks.

Given the popularity of smartphones among young adults and the considerably higher download rates of commercially developed apps compared to research-based apps, there is a need to design pragmatic studies that evaluate commercial tobacco cessation apps. This study aims to fill this gap by combining the advantages of traditional industry-developed software with the benefits of a comprehensive, research-focused feasibility trial.

Moreover, while human-computer systems, including smartphone apps, are usually built to focus on principles of interface design and user engagement [14, 15], this study also offers the opportunity to systematically study the use of an app to understand why it might be effective based on known behavior change theories, techniques, or mechanisms.

### Study objectives

The primary aim of this pilot study is to assess the impact on tobacco cessation of using a smartphone app compared with usual care. The secondary aim is to generate feasibility data to provide the necessary information to inform a future fully powered clinical trial.

## Methods

### Trial design

We will conduct an open randomized controlled trial (RCT) with parallel groups. For additional information on this study’s compliance with Standard Protocol Items: Recommendations for Interventional Trials (SPIRIT), see Fig. 1 and Additional file 1.

**Fig. 1 Fig1:**
[figure not shown]
Standard Protocol Items: Recommendations for Interventional Trials (SPIRIT) schedule of enrollment, interventions, and assessments

### Participants

Participants will be recruited from hospitalized patients from UPMC Montefiore, a large, general hospital located in the mid-Atlantic region of the USA. When patients are admitted, the clinical staff document patient smoking status. Members of the hospital’s Tobacco Treatment Service (TTS) receive a daily list of newly admitted patients who are smokers and attempt to provide approximately 20 min of bedside counseling. A study research staff member will ask permission to shadow the TTS counselor during the session. At the end of the counseling session, if a patient is motivated to quit smoking and meets the inclusion criteria, the research staff member will describe the study, assess eligibility, obtain informed consent (see Additional file 2), collect baseline data, and assign the patient to a study arm. The inclusion criteria are: young adult smoker, aged 18–30 years, interested in cessation, smoked > 5 cigarettes/day over the past 30 days, and must own an Apple or Android smartphone. Potential participants will be excluded if they are already receiving pharmacological and/or behavioral intervention or counseling for tobacco cessation, are unable to provide informed consent, or do not speak English. Participants will be compensated US$25 for completion of each survey for a total of US$50.

### Recruitment

Over a 6-month period, we will recruit 40 young adult smokers aged 18–30 years who are interested in smoking cessation. Participants will receive a TTS counseling session focused on motivational interviewing and then be randomized 1:1 to either standard patient-initiated follow up (through the state Quitline) or use of the Kwit app for 1 month. Participants will be stratified by sex at a 1:1 ratio (10 male and 10 female participants in each group) because men and women are known to have highly variable responses to existing tobacco control interventions [16]. The recruitment procedure will follow existing processes currently being implemented by the TTS. In FY2016, there were 3078 everyday smokers that consented to receive TTS counseling and additional follow up. Of that population, 363 (11.8%) were aged 18–30 years. Therefore, a 6-month recruiting period would expect to identify approximately 181 potential young adult smokers to meet the eligibility criteria. Stratification by sex as planned is highly feasible because roughly half of all TTS-identified individuals were male. While the recruitment of 40 individuals from about 181 who are eligible (22%) seems highly feasible to the TTS team, we have developed contingency plans for recruitment should numbers fall short. Individuals will be compensated for their time to participate in follow-up interviews at the end of 1 month.

### Sample size

Given this is a feasibility trial, a formal sample size calculation is not appropriate [17]. For the current study, we are informed by quantitative usability-testing recommendations that suggest a sample size of 20 [19]. Because we wish to stratify by birth sex, we obtained our sample size of 40 individuals. While we expect this to be more than sufficient, we will remain flexible in our approach and will recruit additional individuals if necessary.

### Randomization

Participants who are eligible will be randomized to either a smartphone experimental group or patient-initiated follow up (usual care) by the research team. They will be stratified by gender, and will be randomized in total using a 1:1 ratio. Neither the participant nor the research team will be blind to their status. An independent statistician will generate an allocation table using Stata’s *ralloc* function. That list will be provided to a member of the research recruitment team, who will upload the table into the Research Electronic Data Capture (REDCap) online survey. Neither the principal investigator (PI) nor any researcher conducting analyses will have access to the randomization process or allocation table. Once recruitment has started, participants that have consented to the study will then be assigned by REDCap to either the experimental or control arms based on the allocation order.

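### The allocation table passes through a member of the recruitment team and only the PI and analysts are barred from it, so concealment is not secured from everyone who may enrol

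*Protocol article*

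**What the plan says.** The Randomization section of the protocol article describes four steps.

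- Generation: "An independent statistician will generate an allocation table using Stata’s *ralloc* function".
- Transfer: "That list will be provided to a member of the research recruitment team, who will upload the table". The destination is REDCap.
- Access: "Neither the principal investigator (PI) nor any researcher conducting analyses will have access to the randomization process or allocation table". No other group is excluded.
- Assignment: "participants that have consented to the study will then be assigned by REDCap to either the experimental or control arms based on the allocation order".

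The same section states that the trial is open: "Neither the participant nor the research team will be blind to their status".

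The Participants section describes entry at the bedside. A research staff member shadows the counselor of the Tobacco Treatment Service (TTS). What happens after counseling depends on a condition: "if a patient is motivated to quit smoking and meets the inclusion criteria". Where it is met, the plan is that "the research staff member will describe the study, assess eligibility, obtain informed consent"; the same person then records the baseline data and assigns the arm.

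**The concern.** Allocation concealment protects the decision to approach and enrol a patient. The people from whom the upcoming assignment most needs to be hidden are those who make or influence that decision. The plan gains independence when the sequence is generated and gives it up at the next step, by sending the whole list to the recruitment team. The stated access bar covers the PI and the analysts and leaves out enrolling staff. This is a rule the article states, so it is more than a detail left to a fuller document.

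Someone who knows the next arm could approach, delay or pass over a patient accordingly, for instance by favouring keener patients when the app is next. The arms would then differ at baseline in motivation, which plausibly affects cessation and retention. Motivation is judged informally here, so later adjustment could not be relied on to remove the imbalance. The Study objectives section names the effect on cessation against usual care as the primary aim. The Power calculations section plans to use the 1-month differences between groups to inform a larger trial.

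**Working it through.** The point concerns procedure, and no power or sample-size figure is contested. The steps below reproduce the one nearby design figure and then follow who can know what, and when.

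**1. The plan's own figure.** The Sample size section takes 20 from usability guidance and stratifies by sex: 20 × 2 = 40. With two arms and two sexes, 40 / 4 = 10 per cell. This agrees with the 10 men and 10 women per group in the Recruitment section.

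**2. Who can know the next assignment.**

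| Person | Sees the table? | Role in entry |
|---|---|---|
| Independent statistician | Yes (generates it) | None stated |
| One recruitment-team member | Yes (receives and uploads it) | Not stated; not excluded from enrolling |
| Other recruiting staff | Not stated; not barred | Screen, consent, assign |
| PI and analysts | Barred | None stated |

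**3. Whether REDCap closes the gap.** REDCap assigns after consent, following the order of the uploaded table. For someone who has not seen that order, the list stays hidden until consent. For someone who has, REDCap only confirms what is already known. Because the research team is not blinded, the list holder can also track the position reached in each sex stratum.

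**4. Predictability.** For the list holder, 40 of 40 assignments (100%) can be known in advance. For comparison, consider someone who knows only the past assignments and guesses the arm with more places left. Under an assumed 10:10 random allocation rule within each sex, the Blackwell–Hodges expected number of correct guesses with n = 10 is

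n + 0.5 × (2^(2n) / C(2n, n) − 1) = 10 + 0.5 × (1,048,576 / 184,756 − 1) = 12.3 of 20, or about 62%.

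With permuted blocks of known size, also assumed, the same formula applied within a block gives:

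- block of 2: 1.5 / 2 = 75%
- block of 4: 2.83 / 4 = 71%
- block of 6: 4.1 / 6 = 68%

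The article states no block size, so these figures only illustrate that holding the list is worse than ordinary guessing in an open trial. The finding does not depend on them.

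**5. Room for selection.** The Recruitment section expects 363 / 2 ≈ 181 candidates in 6 months and plans to enrol 40, and 40 / 181 = 22%. About 181 − 40 = 141 would not be enrolled, so a choice about whom to approach, or when, would leave little trace. That pool is counted on everyday smoking and age only; the other entry criteria would reduce it.

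**The case against.** The strongest reply is that the article names one person and one task. It does not say that the uploader screens, consents or enrols, or that other recruiters see the list. The sequence is generated independently, and REDCap assigns only after consent. The TTS counselor runs the bedside session, and the text does not say who judges motivation. The article also condenses a longer protocol, which may name an uploader with no enrolling role.

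Much of this stands, and it limits the point. A reader might infer that every recruiter knows the next arm before approaching a patient; the text does not support that. What remains is that the uploader is drawn from the recruitment team, nothing excludes that person from enrolling, and the access rule omits enrolling staff.

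A reader might also infer that all three primary feasibility outcomes are biased. That goes too far. Recruitment is a rate for the whole trial and app engagement exists only in the app arm, so neither is a comparison of arms, which is where loss of concealment chiefly acts. Selecting app-friendly patients could still inflate engagement.

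Finally, the analysis is primarily descriptive and the trial is a small pilot. This lowers the stakes but does not remove them, since the trial randomizes and states a comparative aim.

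**Conclusion.** The point holds in this limited form: as written, concealment is not secured from at least one person who may screen, consent or enrol. It rests on two readings of the Randomization section: that the uploader belongs to the recruitment team, which is stated, and that this person may take part in enrolment, which is neither stated nor excluded.

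The main exposure is the 1-month comparison between arms, for the cessation aim and for retention by arm. Possible inflation of app-arm engagement comes second.

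The size of any bias cannot be derived from the documents. It is tempting to reason that steering three patients would alter 3 / 20 = 15% of an arm. That is a share of patients under an invented scenario and not a shift in any outcome, and the article states no expected difference in retention or abstinence to set it against. The 100% in the working describes what the list holder could know; it is no evidence that anyone acted on it.

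**What to change.** Have the independent statistician, or a REDCap administrator with no recruiting role, upload the table directly. Extend the access bar so that it covers everyone who screens, consents or enrols, alongside the PI and analysts. Keep the planned order of eligibility, consent, baseline data and then assignment.

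The Trial status section reports that recruitment began in June 2018 and is ongoing. If a recruiter already holds the list, transferring custody of it does not undo what that person has seen. The statistician should therefore generate a fresh sequence, within sex strata, for the remaining participants, and no recruiter should see it. The alternative is to keep the list holder out of enrolment for the rest of the trial. In either case, report the date of the change and how many participants were assigned before it.

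The cost is small: a different uploader, one added line on access and, mid-trial, a one-time reissue of the sequence. The statistician and REDCap are already in place, and the sample size does not change. Assignments made before the change cannot be protected in retrospect.

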### Intervention

The Just Kwit! study has two arms (see Fig. 2). For the intervention arm, the Kwit app will be installed on the participant’s phone by a research team member. The team member will help the participant create an account and explain the functions of the Kwit app. App use will be tracked for the 30 days between the baseline and follow-up surveys. The control arm is the current standard of care, which is a TTS consult with patient-initiated follow ups after discharge.

**Fig. 2 Fig2:**
[figure not shown]
Patient participation flowchart for the Just Kwit study

In choosing a smartphone app for this study, the selection criteria were (1) available for both Apple and Android; (2) well-rated in both platforms (i.e., 4+ stars); (3) at least 100,000 downloads; (4) features that are comparable to other available apps; and (5) the development team would be willing to have an open collaboration both in data sharing and software development. The Kwit app matched each criterion; it is one of the few cessation apps that is available for download for both Apple and Android. Kwit is highly rated in both online stores, scoring 4.5/5 for Apple and 4/5 for Android. It has been downloaded 100,000–500,000 times on Android phones (Android releases only ranges for downloads). Kwit combines several popular features of tobacco cessation apps, including game-like features (e.g., unlocking achievement milestones for completing cessation-related tasks), useful statistics (e.g., money saved), and an ability to share progress with friends. Users can actively engage with the app to track cravings or view progress, such as life expectancy gained. A passive component notifies users when milestones have been achieved (e.g., when blood no longer contains nicotine). Motivational messages can be actively requested at any time; they can also appear unsolicited, such as when the user logs cravings. The basic app is free, although users are able to purchase additional features, such as removing ads, if so desired.

As with other commercially developed tobacco cessation apps, Kwit development was not informed by evidence-based practices: its features were based on personal experience and user feedback. However, the two aims of this study will provide data to identify which components are most promising, and if health behavior-change mechanisms can help explain their effect. Connecting to a model of behavior change is important as we seek to modify behaviors among young adults. For example, the motivational messages might be closely tied to motivational enhancement therapy, while the money or lifespan trackers might be related to self-monitoring.

### Outcomes

As this study seeks to assess feasibility, the primary data will include (1) recruitment rates, (2) retention rates, and (3) adherence, measured through user engagement with the app. High usability measures correlate strongly with effective interventions [20]. Engagement with the app will be measured using both survey data in conjunction with logged data from the app itself. Logged data will include specific features that are used as well as patterns of activity (e.g., checking the current money saved after viewing a motivational message). We are particularly interested in the use patterns of two popular features in many cessation apps: calculator and calendar. Measures of usability are based on principles from ubiquitous computing guidelines [21]. These concepts will include (1) attention (e.g., “How many times did you use Kwit per day?”); (2) trust (e.g., “Were you able to complete tasks with ease?”); (3) conceptual model (e.g., “Did Kwit behave as expected?”); (4) interaction (e.g., “Was Kwit frustrating to use?”); and (5) impact (e.g., “How comfortable were you using Kwit in social settings?”). Following guidelines for evaluating the usability of medical applications [22], responses will be either yes/no, or chosen from a Likert scale of 1–9 (a longer Likert-type scale was selected to minimize the risk of a ceiling effect). These questions will be paired with open-ended qualitative questions and comments that will complement numerical ratings. For example, an interaction question will first ask the user: “Was Kwit frustrating to use?” with a 1–9 Likert scale option, followed by the open-ended question: “Please describe an example of how Kwit was frustrating to use.”

### Data collection and management

Data will be collected by a member of the study team both on paper and using the REDCap tools hosted at the University of Pittsburgh [23]. REDCap is a secure, web-based application designed to support data capture for research studies, providing (1) an intuitive interface for validated data entry; (2) audit trails for tracking data manipulation and export procedures; (3) automated export procedures for seamless data downloads to common statistical packages; and (4) procedures for importing data from external sources. Consent documents, payment information, and eligibility screening documents will be in paper form. The two surveys administered in this study, the baseline and the follow up, will be completed within REDCap. The baseline survey will be administered to the patient bedside by a member of the research team directly following enrollment and consent. The follow-up survey will be provided to the participant via email, phone, or in person, depending on the participant’s preference. Only members of the research team will have access to the collected data.

The PI has the primary responsibility for study monitoring. Given the nature of the trial (i.e., brief, limited feasibility), there being no access to protected health information, and there being a limited amount of personal information being collected, no formal data monitoring committee will be convened. Quarterly assessments will be made of data quality and timeliness, participant recruitment, accrual and retention, participant risk/benefit ratio, protection of confidentiality of information, and any other factors that affect the study. The Institutional Review Board (IRB) will be informed immediately on a case by case basis of any adverse outcomes, while requests for modifications of the protocol will be submitted to the IRB on a quarterly basis. Confidentiality of the data and the results of monitoring will be protected.

